**Quantitative part**										
	Demographic data	Yes	No	No	Questionnaire		Once		Sex Ethnicity Age Highest education status Job category Monthly salary Smoking history Background illness	
	Weight	Yes	Yes	Yes	SECA Electronic Column Scale (SECA GmbH and Co KG)		Twice in kg, to the nearest 0.1 kg		BMI in kg/m2, categorized based on Asian population standard	
	Height	Yes	Yes	Yes	SECA Electronic Column Scale		Twice in cm, to the nearest 0.1 cm		BMI in kg/m2, categorized based on Asian population standard	
	Waist circumference	Yes	Yes	Yes	SECA measuring tape (SECA)		Twice in cm, to the nearest 0.1 cm		Waist-to-hip ratio based on the World Health Organization cutoff points	
	Hip circumference	Yes	Yes	Yes	SECA measuring tape		Twice in cm, to the nearest 0.1 cm		Waist-to-hip ratio based on the World Health Organization cutoff points	
	Blood pressure	Yes	Yes	Yes	An automated upper arm device (Omron Automated Blood Pressure Monitor; HEM 7130)		Twice (third measure if error reading or if one value outside normal range)		Systolic and diastolic blood pressure in mm Hg	
	Body composition	Yes	Yes	Yes	InBody 770 analyzer (Biospace)		Once		Body fat % Body fat mass, kg Skeletal muscle mass, kg	
	Quality of life	Yes	Yes	Yes	Obesity and Weight-Loss Quality of Life Questionnaire		Once		Self-reported quality of life in the past month	
	Physical activity	Yes	Yes	Yes	International Physical Activity Questionnaire-Short Form		Once		Self-reported physical activity for the past week, in metabolic equivalent task minutes per week	
	Dietary intake	Yes	Yes	Yes	Food Frequency Questionnaire		Once		Self-reported dietary intake for the past month	
	Biochemical testing	Yes	Yes	Yes	Liquid chromatography (Adams A_1c_ HA-8160; Arkray Inc); automated analyzer (Dirui CS-400)		Once		Fasting blood glucose 2-hour postprandial blood glucose Hemoglobin A1c Fasting lipid profile^b^ Fasting insulin	
**Qualitative part**										
	Readiness to participate in screening	Yes	No	No	Behavioral contract and informed consent		Once, during recruitment phase		N/A^c^	
	Focus group discussion	No	No	Yes	Predetermined outlined interview guide with probes; an audio recorder		Once, after unsupervised intervention phase at the end of month 6		Themes generated from codes from each category	

^a^Measurements were carried out by trained research staff using standard protocols.

^b^Fasting lipid profile parameters: total cholesterol, triglycerides, low-density lipoprotein cholesterol, and high-density lipoprotein cholesterol.

^c^N/A: not applicable.

### Training of Study Team

Before the beginning of data collection, a 3-day workshop was conducted to train the research team members on the skills needed during data collection. The training included techniques for anthropometric measurements, body composition measurements using the InBody 770 analyzer, and explanation on questionnaires used in the study. Presentation on data collection workflow, intervention supervision processes, and biochemical testing procedures was also included in the training. In addition, selected study members were trained by a psychologist from the Institute for Behavioral Research on conducting readiness to participate in screening during the recruitment phase.

### Data Management

To ascertain that data collection and record keeping are conducted efficiently, a data collection booklet was developed and assigned to each participant in this study. This booklet consisted of 5 sections (sociodemographic, quality of life, physical activity, dietary record, and anthropometry measurements) sorted into 3 parts representing each point of data collection: baseline, month 3, and month 6. This booklet was used as a data-collection tool to record the responses and measurements of the participants.

The data recorded in the booklet were entered into a database at the end of the study. The data cleaning procedure was conducted by crosschecking all the entered data in the database and booklet and exploring the data to detect any significant outliers that possibly resulted from measurement errors or data entry.

Data for qualitative part were collected using an audio recorder, and each recording was transcribed verbatim by the qualitative team. Each transcript was checked by an independent member and confirmed by a transcriber and interviewer. Consent for audio recording was obtained before the interviews.

### Data Analysis

Analysis was conducted using the SPSS software (version 25; IBM Corp). Data for continuous variables were presented as mean (SD) or as median (IQR) for nonnormally distributed data. For categorical variables, frequencies were calculated and are presented as percentages. Variables were compared using the independent 2-tailed *t* test or Mann-Whitney *U* test for continuous variables and the chi-square or Fisher exact (n≤5 in any cell) test for categorical variables. All statistical tests were 2-sided, and the significance level was set at *P*<.05. In further analysis, repeated measures ANOVA will be used to compare the within- and between-group changes in the outcomes, adjusted for possible confounders such as age, ethnicity, and gender.

Data from the FGDs were analyzed using thematic analysis. Interviews transcribed verbatim were independently read by a qualitative researcher ([name]) to identify the preliminary codes. An interpretivist approach was taken to interpret and code participants’ experiences for the entire study. In this way, the coding of participants’ feedback was performed without assumptions or subjective interpretation by the researchers. Meaning units were reviewed, identified, and sorted into codes, before grouping them into categories. Finally, through consensus, the content of each category group was summarized and grouped into main themes. The best representative participants’ quotes for each theme were chosen to support the results. Thematic analysis was used, where initial open codes were generated from the data, after which the codes were organized into larger themes.

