### Study Procedure

#### Quantitative Method

##### Data Collection

During the 6-month study duration, data collection was conducted at 3 points: baseline (before starting the supervised phase), month 3 (at the end of the supervised phase), and month 6 (at the end of the unsupervised phase). Participants were asked to answer questionnaires on social demography (during baseline only), the Food Frequency Questionnaire (FFQ), the International Physical Activity Questionnaire-Short Form (IPAQ-SF), and the Obesity and Weight-Loss Quality of Life (OWLQOL) Questionnaire. Anthropometry measurements and fasting blood samples were taken. Oral glucose tolerance test and body composition analysis were also performed.

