## Results

### Study Participants

A total of 302 volunteers were interested in joining the study and underwent the screening process. After screening for BMI and eligibility during the first stage of recruitment, of 302 volunteers, only 203 (67.2%) were found eligible. Most volunteers were excluded owing to a BMI of <23 kg/m^2^ or having chronic diseases on medication, such as diabetes mellitus and hypertension. During the readiness to participate in screening (stage 2 recruitment phase), 27 volunteers were excluded for various reasons but were not limited to reasons such as commitment issues, furthering education, or moving away. Hence, there were a total of 177 participants recruited in this study; 91 (51.4%) in the IFHP group and 86 (48.6%) in the HP group (Figure 1). During the supervised intervention period, 28 participants withdrew from our study in both groups (IFHP: 16/28, 57%; HP: 12/28, 43%), whereas 27 withdrew during the unsupervised period (IFHP: 12/27, 44%; HP: 15/27, 56%). The reasons for withdrawal included pregnancy (13/55, 24%), inability to commit to study intervention (24/55, 44%), transfer to a different workplace (8/55, 15%), being diagnosed with hypertension, diabetes, hypercholesterolemia on medication (5/55, 9%), and other reasons (5/55, 9%). There were 63 and 59 participants who completed the study in the IFHP and HP groups, respectively.

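### Repeated measures ANOVA over three visits would by default analyse at most 122 of 177 participants and discard the month-3 data of up to 27 later leavers

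*Protocol article*

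**What the plan says.** Data Analysis names SPSS version 25 and says that "repeated measures ANOVA will be used to compare the within- and between-group changes in the outcomes". It gives age, ethnicity and gender as examples of covariates. The wording is in the future tense. The section mentions no mixed model and no imputation.

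Data Collection fixes the visits: "data collection was conducted at 3 points: baseline (before starting the supervised phase), month 3 (at the end of the supervised phase), and month 6".

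Study Participants gives the flow: "a total of 177 participants recruited in this study; 91 (51.4%) in the IFHP group and 86 (48.6%) in the HP group". The supervised phase lost 28 people (16 IFHP, 12 HP). On the second phase the article says "whereas 27 withdrew during the unsupervised period"; of these, 12 were in IFHP and 15 in HP. Completers number 63 and 59. The reasons for the 55 withdrawals are inability to commit (24), pregnancy (13), workplace transfer (8), a new diagnosis of hypertension, diabetes or hypercholesterolemia on medication (5) and other (5). They are not split by arm or by phase.

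**The concern.** Classical repeated measures ANOVA needs a complete set of visits for each person, and SPSS by default removes anyone with a gap. Two things follow.

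First, measurements already taken are wasted. Someone who finished the supervised phase and left later would be removed from the month-3 comparison as well as the month-6 one.

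Second, the analysed group consists of those who stayed. Five people left because of a new diagnosis in the cardiometabolic domain that the study measures, and 24 because they could not commit to the intervention. If such people did worse, average change among completers looks better than average change among all who started. Principal Findings hypothesises improvement within the IFHP group at 3 and 6 months, and Future Directions asks whether changes last through the unsupervised phase. An analysis that omits everyone who left in that phase is poorly suited to both questions.

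**Working it through.** **Assumptions.** All three visits enter one classical ANOVA with no prior imputation; every completer has every visit; all 27 late leavers attended month 3. The documents state none of these outright, so 122 and 149 are upper limits.

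**1. Counts (Study Participants).**
- Analysed: 177 − 28 − 27 = 122 = 63 + 59; 122/177 = 68.9%.
- Dropped: 55/177 = 31.1%. The reasons also sum correctly: 24 + 13 + 8 + 5 + 5 = 55.
- Available at month 3: IFHP 91 − 16 = 75; HP 86 − 12 = 74; total 149.
- Baseline only: 28.

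**2. The plan's own sample size (Sample Size).** With a difference of 5, SD 10, two-sided α = 0.05 and 80% power, n per arm = 2(1.96 + 0.842)²/(5/10)² = 62.8, so 63. The t-based version gives 63.8, so 64, which is the plan's figure. The same standardised effect of 0.5 is used below.

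**3. Month-3 precision.**
- SE ratio = √[(1/63 + 1/59)/(1/75 + 1/74)] = √(0.03282/0.02685) = 1.106.
- Power of a two-sample t test at 0.5: 78.2% with 63/59; 85.8% with 75/74.

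**4. Loss by arm and by reason.**
- IFHP 28/91 = 30.8%; HP 27/86 = 31.4% (Fisher p = 1.0).
- Clearly related to outcome: 5 of 55. Adding those unable to commit: at most 29 of 55, which is 16.4% of 177.
- Pregnancy and transfer: 21 of 55, with no evident link to success.

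**5. Illustration of bias.** The withdrawal fractions are those reported. The rest is assumed: SD 10, correlation 0.8 between visits, true percentage weight change at month 6 of −5 (IFHP) and 0 (HP), so a true difference of −5. Where dropout depends on outcome, those with less loss are more likely to leave.

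| Dropout | Completers, IFHP / HP | Completer difference | Likelihood difference |
|---|---|---|---|
| Unrelated to outcome | −5.03 / −0.01 | −5.02 | −5.01 |
| Late dropout depends on month-3 result, both arms | −6.66 / −1.99 | −4.67 | −5.04 |
| Same, IFHP only | −6.66 / 0.02 | −6.68 | −5.04 |
| Same, HP only | −5.03 / −1.99 | −3.04 | −5.04 |
| Depends on unseen values, both arms | −8.60 / −3.74 | −4.85 | −5.09 |

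The HP-only row combines the IFHP result of the first row with the HP result of the second: −5.03 − (−1.99) = −3.04. Its likelihood difference is formed in the same way.

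Within-arm change is overstated wherever those with less loss leave. The between-arm difference can be nearly right, too large or too small, depending on which arm has the selective loss. In the last row the likelihood estimates within arms remain wrong (−7.62 and −2.53), although their difference is close to the truth.

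**The case against.** **An analysis plan that is not shown may deal with this.** Analysis populations and imputation are often placed there. The article states no completer population and does not rule out imputing before the ANOVA. This stands in part: the loss of 55 people is the default consequence of the named method, not a declared exclusion. The choice of method is nevertheless stated, and a better one is available in the same software.

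**A reader might infer that the ANOVA biases the study toward those who succeeded, or inflates the fasting effect.** The documents do not support that. Total loss is almost identical in the two arms, reasons are not reported by arm, and no outcome data are given by dropout status. Inflation appears in the illustration only if selective loss is confined to IFHP, and nothing reported suggests this: late withdrawals were fewer in IFHP (12) than in HP (15). Selective loss in HP only would shrink the difference instead.

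**The remedy is partial.** This stands. At most 27 of the 55 would add follow-up data. The 28 early leavers have baseline only, and a likelihood model does not remove bias from dropout that depends on unseen values. Nor does it make a study allocated by institute into a randomised comparison.

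**Power is not the main problem.** This also stands. Completers give about 78% against a planned 80%, and the plan allowed for 40% attrition when 31% occurred. The 11% figure concerns month 3 only.

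**Conclusion.** The point holds in a limited form. With 31% attrition already known, the named method would by default use 69% of participants and discard the month-3 data of up to 27 of them. At month 3 this costs about 11% in standard error and about 8 points of power (86% to 78%), if all late leavers were measured then. Within-group improvement in completers may be overstated, because up to 29 withdrawals may be connected with outcome, though only 5 clearly are. Bias between arms is a possibility whose presence and direction the article does not allow anyone to judge. The method should be changed before the outcome analysis. The point gives no ground for calling the between-group result wrong.

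**What to change.** In Data Analysis, replace repeated measures ANOVA with a likelihood-based linear mixed model for repeated measures (SPSS MIXED): group, visit, group × visit, the covariates already planned and an unstructured covariance, using every available visit. Read the month-3 and month-6 group contrasts from that model.

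State two limits beside it: the 28 early leavers contribute baseline only, and the model assumes that dropout depends on observed data. Add a sensitivity analysis for outcome-related dropout, for example giving unfavourable values to those who left through inability to commit or a new diagnosis on medication. Tabulate withdrawal reasons by arm, and keep any completer analysis as supportive.

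The cost is revised wording and a little more analysis work. No new data are needed.

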### Ethics Approval and Informed Consent

Ethics approval for this study has been obtained from the Medical Research & Ethics Committee, Ministry of Health Malaysia (NMRR-19-3261-51726). Before recruitment, written informed consent was obtained from each participant, including the storage of samples for biochemical and future DNA analyses. Participants were also informed that future research will be related to medical conditions and current interventions and that their privacy will be protected. Before enrollment, all participants were fully informed of the potential risks associated with engaging in this study. They were free to withdraw from the study at any time during their participation. This study was conducted in full conformity with the current revision of the Declaration of Helsinki and International Council for Harmonisation Guidelines for Good Clinical Practice.

## Results

### Study Participants

A total of 302 volunteers were interested in joining the study and underwent the screening process. After screening for BMI and eligibility during the first stage of recruitment, of 302 volunteers, only 203 (67.2%) were found eligible. Most volunteers were excluded owing to a BMI of <23 kg/m^2^ or having chronic diseases on medication, such as diabetes mellitus and hypertension. During the readiness to participate in screening (stage 2 recruitment phase), 27 volunteers were excluded for various reasons but were not limited to reasons such as commitment issues, furthering education, or moving away. Hence, there were a total of 177 participants recruited in this study; 91 (51.4%) in the IFHP group and 86 (48.6%) in the HP group (Figure 1). During the supervised intervention period, 28 participants withdrew from our study in both groups (IFHP: 16/28, 57%; HP: 12/28, 43%), whereas 27 withdrew during the unsupervised period (IFHP: 12/27, 44%; HP: 15/27, 56%). The reasons for withdrawal included pregnancy (13/55, 24%), inability to commit to study intervention (24/55, 44%), transfer to a different workplace (8/55, 15%), being diagnosed with hypertension, diabetes, hypercholesterolemia on medication (5/55, 9%), and other reasons (5/55, 9%). There were 63 and 59 participants who completed the study in the IFHP and HP groups, respectively.

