#### Sample Size

Sample size calculation was conducted using a power and sample size program. It followed the rules required for comparison between the 2 groups [13]. The sample size was estimated using the level of significance (α=.05) and power of the study (1-β=.80), minimum suggested difference (delta) of 5% (SD 10%) weight loss that may be achieved under this intervention, and the corresponding differences among groups. The assumption of 5% weight loss used in the sample size calculation was based on a review conducted by Ryan and Yockey [14], which stated that a minimum weight loss of 5% is needed to improve cardiometabolic risk such as hypertension, diabetes mellitus, and hyperlipidemia. The minimum sample size required for this study was 64 participants. Considering 40% attrition, the required sample size for each arm was 90 participants. A total of 180 participants were required for this study.

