### Future Directions

Adherence to dietary interventions is essential to ensure the validity of research findings and, most importantly, to ascertain the sustainability of the desired outcomes beyond the research period. As described by the World Health Organization, adherence is “the extent to which a person’s behavior-taking medication, following a diet, and executing lifestyle changes, corresponds with agreed recommendations from a health care provider” [28]. In this study, we examined the elements of adherence in both quantitative and qualitative parts. Quantitatively, we investigated adherence to intervention and sustainability of outcomes’ changes in the unsupervised intervention phase. We measured the outcomes at the end of the phase and compared them with those of the previous 2 parameters. In the qualitative part, we assessed readiness to participate in screening during the recruitment phase, in which the motivation and readiness to comply with intervention protocols were assessed. In addition, FGDs were conducted at the end of the study to explore the participants’ experiences while undergoing the intervention, including barriers and enablers that influence their adherence to the diet protocols.

We plan to disseminate the study results to collaborating institutes and organizations, study participants, and respective stakeholders. These findings will be submitted to 2 peer-reviewed journals and presented at academic conferences.

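### Up to 37 of 55 withdrawals were for reasons that do not by themselves prevent measurement, and a conventional three-visit repeated measures ANOVA would describe only the 122 who stayed

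*Protocol article*

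**What the plan says.** The protocol article's Results (Study Participants) report 177 people allocated: 91 to intermittent fasting plus healthy plate (IFHP) and 86 to healthy plate alone (HP). Of these, 55 withdrew: 28 in the supervised period (16 IFHP, 12 HP) and 27 in the unsupervised period (12 IFHP, 15 HP). Besides 13 pregnancies and 5 other reasons, the article lists "inability to commit to study intervention (24/55, 44%), transfer to a different workplace (8/55, 15%), being diagnosed with hypertension, diabetes, hypercholesterolemia on medication"; this last reason accounts for 5. It then states: "There were 63 and 59 participants who completed the study in the IFHP and HP groups, respectively".

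Data Analysis names one model for the outcomes, a repeated measures ANOVA for changes within and between groups, adjusted for confounders such as age, ethnicity and gender. Data Collection sets three visits: baseline, month 3 and month 6.

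The Abstract and Conclusions give effectiveness as the aim. Future Directions adds adherence and the durability of change through the unsupervised phase: "We measured the outcomes at the end of the phase and compared them with those of the previous 2 parameters". Ethics Approval and Informed Consent says that participants could leave whenever they wished.

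**The concern.** A person who can no longer keep to a diet, who moves to another workplace or who starts treatment for a new diagnosis can in principle still be weighed and can still fill in a questionnaire. The article nevertheless reports all three as withdrawals from the study. The first reason concerns the diet itself. The third concerns blood pressure, glucose and lipids, which are study outcomes.

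If the outcome analysis then rests on people seen at all three visits, it rests on a group selected partly by how tolerable the diet was and partly by how their cardiometabolic measures developed. For a study of effectiveness and sustainability, stopping the diet is part of the answer. An estimate in those who stayed answers a different question, and it could differ from the effectiveness estimate in either direction.

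**Working it through.** **Inputs.** All counts are from Results, Study Participants. The design assumptions are from Sample Size ("level of significance (α=.05) and power of the study (1-β=.80" and "minimum suggested difference (delta) of 5% (SD 10%) weight loss") and Data Analysis ("All statistical tests were 2-sided").

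**1. The article's own figures.**
- Reasons: 13 + 24 + 8 + 5 + 5 = 55. Phases: 28 + 27 = 55.
- Completers: 91 − 28 = 63 and 86 − 27 = 59, total 122.
- Sample size: a two-sided two-sample t test with difference 5, SD 10, alpha 0.05 and power 0.80 needs 63.77, so 64 per arm. This agrees with "The minimum sample size required for this study was 64 participants" read as a per-arm figure.

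The counts are consistent.

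**2. Withdrawals whose reason does not itself prevent measurement.**
- 24 + 8 + 5 = 37, and 37/55 = 67%.
- This is an upper bound, because the article does not say how many would have agreed to further visits or could have been reached.

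**3. Who a conventional analysis would use.**
- A repeated measures ANOVA over three visits, run conventionally, drops anyone with a missing visit: 122/177 = 69%.
- Those who left in the unsupervised period did so after month 3, so up to 91 − 16 = 75 IFHP and 86 − 12 = 74 HP participants, 149 in all (149/177 = 84%), may have month-3 data.
- Had all 37 been measured at month 6, the number would have been 122 + 37 = 159 (159/177 = 90%).
- At difference 5 and SD 10, power is 78.2% for 63 against 59. It would be 87% to 88% with the 37 included, whatever their split between arms.

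**4. Balance.** IFHP lost 28/91 = 30.8% and HP 27/86 = 31.4%. The numbers are balanced. The text shown does not give reasons by arm.

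**5. How far the difference could move.** For illustration only, assume that completers lose 5% of weight in IFHP and 3% in HP, a gap of 2.0 points, and that the 24 who could not commit lose nothing. Let j of the 24 be in IFHP:

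gap = 5 × 63/(63 + j) − 3 × 59/(59 + 24 − j)

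| Split of the 24 | IFHP | HP | Gap (points) |
|---|---|---|---|
| All in IFHP (j = 24) | 5 × 63/87 = 3.6 | 3.0 | 0.6 |
| Even (j = 12) | 5 × 63/75 = 4.2 | 3 × 59/71 = 2.5 | 1.7 |
| All in HP (j = 0) | 5.0 | 3 × 59/83 = 2.1 | 2.9 |

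Both extremes fit the reported totals. With all 24 in IFHP, 28 = 24 + 4, and the other 31 withdrawals are 4 + 27. With all 24 in HP, 27 = 24 + 3, and the other 31 are 3 + 28.

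Giving zero loss to the other 13 (8 transfers and 5 diagnoses) as well changes both ends:
- All 24 in IFHP: 0 to 4 of the 13 can be in IFHP. The gap runs from 315/91 − 177/68 = 0.9 to 315/87 − 177/72 = 1.2.
- All 24 in HP: 10 to 13 of the 13 must be in IFHP. The gap runs from 315/76 − 177/83 = 2.0 to 315/73 − 177/86 = 2.3.

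**The case against.** The strongest reply is that a stated reason for leaving does not show willingness to be measured. Participants were free to go, no rule for removing people is shown, and the eligibility criteria are worded for entry only. A reader might infer that the study took non-adherers or newly treated people out of follow-up. The article does not say so. It also does not say when or where the five diagnoses were made, so it does not support the reading that the study's own month-3 tests led to them. This stands, and it is why 37 is a ceiling.

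A reader might also infer that the trial result describes only people who kept to the diet. That goes too far. No outcome result is reported and no completers-only analysis set is declared. Completing is also not the same as adhering: the unsupervised phase had no reminders, fasting records or meal pictures, so someone could stop the diet and still attend at month 6.

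Losses are nearly equal between arms and below the planned allowance: "Considering 40% attrition, the required sample size for each arm was 90 participants". That protects the numbers but not the comparison, since equal counts can hide different reasons. The reasons by arm may be in the participant flow chart, which is not shown. Analysis sets and missing-data handling may be set out in the full protocol or analysis plan, so their absence from an article is not the complaint. What remains is that the one model the article names, run in the usual way, meets a pattern of loss that it reports as partly due to the diet and to outcome-related diagnoses.

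**Conclusion.** The concern holds in this form. Up to 37 of 55 withdrawals (67%) were for reasons that do not by themselves rule out measurement, the 24 who could not commit being the clearest case. A repeated measures ANOVA restricted to complete data would rest on 122 of 177 (69%) and would estimate the effect in those who stayed.

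The direction of bias cannot be determined from the text. The range of about 0.6 to 2.9 points around a completer gap of 2.0 depends on the assumed 5% and 3% losses, zero loss in the 24, and the two extreme splits between arms. It shows how much is undetermined and is not an estimate of bias. A claim that the effect must be overstated would not be supported, because the split that widens the gap is as feasible as the one that shrinks it.

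**What to change.** - Analyse all allocated participants with any available visit, for example with a mixed model for repeated measures, so that month-3 data from those who left later are used. This helps only in part. It does not replace month-6 values that are missing because of the diet or the outcome, so the sensitivity analysis below is also needed.
- Label any complete-case result as the effect in completers.
- State whether the 37 were offered further visits, and report withdrawal reasons by arm and phase.
- Add a sensitivity analysis that gives the 24 who could not commit no change from baseline, each in the allocated arm.
- Report the five new diagnoses on medication by arm as cardiometabolic outcomes, not only as withdrawals.

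Weighing those who left now would not help, because it would not measure the month-6 outcome. The cost is a little more analysis work and an estimate that may be less favourable. No new data collection is needed.
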